## Abstract

**Background:**

Perinatal substance use can have significant adverse effects on maternal and child health and family stability. Few interventions are specifically designed to address this significant public health problem. The Parent–Child Assistance Program (PCAP) is a 3-year case management and home-visiting intervention that seeks to help birthing persons with at-risk substance use during pregnancy to achieve and maintain substance use disorder recovery and avoid exposing future children to substances prenatally. At-risk refers to a level of substance use that creates problems in the individuals’ lives or puts them or their children at risk of harm either prenatally or postnatally. Although the program has consistently shown substantial pre- to post-intervention improvements in its participants, PCAP remains to be tested with a rigorous randomized controlled trial (RCT). This study protocol describes a randomized controlled trial that aims to examine the effectiveness of the intervention compared to services as usual in affecting primary outcomes related to substance use and family planning. Secondary outcomes will concern connection to recovery support services and family preservation.

**Methods:**

Using an intent-to-treat design, the study will recruit from two metro areas in Oklahoma and enroll 200 birthing individuals who are pregnant or up to 24 months postpartum with at-risk substance use during their current or most recent pregnancy. Participants will be randomly assigned, stratified by location, to receive either PCAP or services as usual for 3 years. Participants in the PCAP condition will meet with their case manager approximately biweekly over the course of the intervention period, in their local communities or in their own homes whenever possible. Case managers will assist with goal setting and provide practical assistance in support of participants’ goals. Primary and secondary outcomes will be assessed at baseline and 12, 24, and 36 months post-baseline using the Addiction Severity Index interview and a self-administered survey.

**Discussion:**

Results from this trial will help to gauge the effectiveness of PCAP in improving parent and child well-being. Results will be reviewed by federal clearinghouses on home-visiting and foster care prevention to determine the strength of evidence of effectiveness with implications for federal financing of this program model at the state level.

**Trial registration:**

ClinicalTrials.gov NCT05534568. Registered on 6/8/2022.

**Supplementary Information:**

The online version contains supplementary material available at 10.1186/s13063-024-08098-6.

## Background {6a}

### Prevalence of perinatal substance use

Perinatal substance use is a significant public health problem associated with adverse maternal [1, 2] and neonatal [3, 4] outcomes. According to the 2022 National Survey on Drug Use and Health, 5.3% of pregnant women reported past month binge alcohol use and 9.6% reported past month illicit drug use [5]. In a 2019 population-based sample of postpartum women, one in 15 (6.6%) self-reported using prescription opioid pain relievers during pregnancy, and of those, one in five indicated misuse [6]. Rates of substance use disorders (SUDs) among pregnant and parenting women are concerningly high, particularly among low-income women. One study examining three state Medicaid programs from 2013 to 2016 found 11.3% of postpartum women had a SUD [7], and an examination of delivery hospitalizations between 2000 and 2018 revealed that the prevalence of SUD diagnoses has been increasing [1]. Among those who achieved abstinence in the last month of pregnancy, rates of relapse can be as high as 80% in the 2 years after delivery [8].

### Poor outcomes from perinatal substance use

Perinatal substance use can have significant adverse effects on maternal and child health. Drug overdose is now a leading cause of death during and shortly after pregnancy. Overdose deaths among pregnant and postpartum individuals increased by 81% from 2017 to 2020 [9], and up to 22% of pregnancy-associated deaths are attributable to substance use [10]. Substance use during pregnancy is linked to decreased prenatal and postpartum care access [11], and the use of opioids or illicit stimulants during pregnancy is associated with a fourfold increase in risk of postpartum readmission [2]. Women with SUDs have a 6.2-fold increased risk of postpartum suicide attempts, and the risk nearly doubles for those with both SUD and psychiatric diagnoses [12].

### Poor outcomes for children

Alcohol use during pregnancy is a leading cause of preventable birth defects [13] and results in fetal alcohol spectrum disorders with lifelong impacts [14] and high costs of care [15]. Prenatal exposure to cannabis, opioids, and stimulants has also been found to have adverse effects on newborns. Cannabis is often believed to be harmless or even beneficial by those who use it during pregnancy [16], yet such use has been linked to lower birthweight, decreased length, and smaller head circumference [17]. Prenatal opioid use is associated with maternal mortality, stillbirth, preterm birth, low birthweight for gestational age, neonatal abstinence syndrome, need for neonatal intensive care, and prolonged hospital stays [18, 19]. Prenatal stimulant use is linked to fetal growth restriction, preterm birth, and low birthweight for gestational age [20, 21].

### Need for effective interventions

Given the scope and impact of perinatal substance use on maternal and child health outcomes, effective interventions to address this problem are sorely needed. Currently under the federal Maternal, Infant, and Early Childhood Home Visiting (MIECHV) program’s clearinghouse—the Home Visiting Evidence for Effectiveness Clearinghouse (HomeVEE)—no programs with strong evidence of effectiveness are targeted specifically to pregnant people or parents with SUDs. Moreover, the number of HomeVEE-rated programs that meet criteria for strong evidence and produce statistically significant results on parental SUDs is meager and limited in scope. At the time of this writing, only Family Spirit [22], Nurse Family Partnership [23], and Healthy Families America [24] have documented significant effects on parental SUD. Only two programs are rated as highly effective for addressing parental SUD to prevent foster care placements under the new clearinghouse for reviewing foster care prevention programs established by the Family First Prevention Services Act of 2018 (FFPSA) (42 USC § 675a).

In this article, we describe a study protocol to evaluate a program specifically designed to address perinatal substance use. The Parent–Child Assistance Program (PCAP) is a 3-year case management and home-visiting intervention for pregnant and postpartum individuals with at-risk substance use during their most recent pregnancy, that is, a level of substance use that creates problems in the individuals’ lives or puts them or their children at risk of harm either prenatally or postnatally. Although individuals completing the program have consistently shown significant pre- to post-intervention improvements, PCAP remains to be tested with a rigorous randomized controlled trial (RCT), often a requirement to be considered an evidence-based program under federal research standards [25, 26]. Therefore, we are conducting a RCT of PCAP within the state of Oklahoma. In state fiscal year 2020, 1,024 newborns who were tested were substance exposed, justifying the target sample size and the need for this project in Oklahoma [27].

## Research design and methods

### Research objectives {7}

The purpose of this RCT is to evaluate the impacts of PCAP on parental recovery, connection to recovery support services, family well-being, and the likelihood of future substance-exposed births. Consistent with our focus on prevention of prenatal substance exposure, this trial focuses on pregnant and postpartum birthing individuals, which includes people with different gender identities who are capable of becoming pregnant.^1^

We hypothesize that individuals receiving the intervention will experience better outcomes than those receiving services as usual in the community over the same 3-year period. Primary outcomes include those related to SUD recovery and the prevention of substance-exposed births. Secondary outcomes include connection to recovery support services, parental custody, criminal justice involvement, and financial stability. The study protocol has been approved by the University of Oklahoma Institutional Review Board, which is responsible for ongoing oversight, the Oklahoma Department of Mental Health and Substance Abuse Services, and the Oklahoma Department of Human Services. The project has received a Certificate of Confidentiality from the National Institutes of Health and is registered on ClinicalTrials.gov.

### Study design {8} {9} {14}

We will evaluate PCAP using a RCT with an intent-to-treat design in two sites in Oklahoma: Oklahoma City and Tulsa, including their surrounding areas. The study will recruit and enroll 200 participants, with 50 control and 50 treatment group participants at each site. Both groups will participate in data collection at baseline and at 12, 24, and 36 months post-baseline, with 36 months post-baseline being the primary endpoint. Study participants will not be constrained from accessing any other services or interventions that may be available in their community.

### Description of the intervention {11a} {11b} {11d}

The Parent–Child Assistance Program (PCAP) has been described in detail elsewhere [25, 28]. In brief, PCAP is a 3-year intervention for pregnant and post-partum individuals with problematic or at-risk substance use during their most recent pregnancy. Built on the theoretical foundations of relational theory [29], the transtheoretical model of behavior change [30], and harm reduction [31], PCAP aims to support birthing individuals in completing SUD treatment and link them with comprehensive community resources to help them stay in recovery, build healthy lives, and avoid exposing any future children to alcohol or drugs prenatally. PCAP provides program participants with a bachelor’s-level case manager (CM), with whom they meet approximately bi-weekly, in participants’ own homes or elsewhere in the community. CMs typically work with up to 20 participants and their families, serve as role models, help them to articulate their own goals and take steps to reach them, and provide transportation and practical assistance when needed in support of participants’ goals. The intervention manual is available at https://pcapwa.org/manual. There are no formal criteria for modifying the intervention for a given participant. The design of the intervention provides for flexibility to adjust the frequency of contacts according to the participant’s needs and preferences while aiming for an average of two face-to-face contacts per month over the course of the intervention. Consistent with the intent-to-treat approach, participants who ask to suspend their participation in the intervention or withdraw from the intervention completely will remain in the study unless they specifically ask to withdraw from the study as a whole.

### Description of the control condition {6b}

Participants randomly assigned to the control condition will not receive PCAP but will not be constrained from accessing available services as usual in their community. They will be provided with a list of local services and resources. These resources include information for accessing substance use disorder and mental health treatment and support, health care, family planning, domestic violence services, housing and food assistance, and legal services.

### Participants and recruitment {15}

The recruitment strategy will leverage a database of service providers that includes SUD treatment facilities, hospitals, birthing centers, judicial personnel, tribal groups, Indian health centers, mental health providers, and other service providers and agencies that may encounter the target population, such as WIC/SNAP/food stamp/welfare offices, emergency rooms/urgent care, homeless shelters, parenting classes, health departments, domestic violence shelters, community health centers (taking Medicaid), Planned Parenthood, and hospital social workers. The database is compiled by research and direct service staff based on their knowledge of service providers in the communities. Recruitment also occurs through public webinars, presentations and vendor tables at local and state conferences and symposia, presentations at local organizations, media attention, flyers, and social media.

### Screening, consent, enrollment {10} {26a} {26b}

Prospective participants may self-refer or be referred by friends, family, or service providers via phone or by completing a referral form on the project Web page. A brief screening conducted by research staff ascertains eligibility. Inclusion criteria are as follows: (1) being pregnant or up to 24 months postpartum, (2) self-reporting at-risk alcohol or drug use during the most recent pregnancy, and (3) lacking adequate connection to community/social/health service providers. Alternatively, consistent with the PCAP model, individuals are eligible if they have a child (of any age) with Fetal Alcohol Spectrum Disorder, continue to use alcohol, and are in their childbearing years. Exclusion criteria include not being able to communicate in English, being under the age 18 years, having a significant cognitive or mental health condition that would preclude the ability to consent to be in the study, and being enrolled in a program that provides duplicative services. Informed consent will be obtained from eligible individuals by the Research Coordinator before administering the baseline data collection instruments. Randomization will occur upon completion of the baseline data collection.

#### Assessment procedures

Whenever feasible, participants will complete study assessments at a private workstation at one of the study sites, connecting with the research coordinator via Zoom videoconferencing. In situations where a participant cannot come to the site, assessments may be conducted with the interview portion via phone and the survey portion completed via web link or on paper forms to be returned via US Mail to the research office. Alerts will be used to remind research staff of data collection intervals. To maintain currency of contact information, research staff will check in with study participants in both groups every 3 months between data collection intervals with a brief online form sent by text message.

### Randomization procedures {16a} {16b} {16c}

Group assignment will occur via an online random assignment generator called Research Randomizer [32], which relies on a computer algorithm for randomization within REDCap, the data management system described below. Randomization will be stratified by location to produce equal numbers of participants in the treatment and control groups at each site. Neither the research staff using the system nor the participant will know the group assignment before the baseline data are collected. Figure 1 displays enrollment and randomization processes.

**Fig. 1 Fig1:**
[figure not shown]
Randomization and enrollment process

### Blinding {17a} {17b}

Group membership will not be blinded after assignment. Participants and staff will be aware of whether a participant is assigned to the treatment or control group by necessity given the nature of the intervention.

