### Data management {19}

Whenever possible, data will be directly entered into REDCap, a HIPAA-compliant data management platform. During the interview portion of the assessment, the research coordinator will enter participant responses into REDCap as they are given. When the self-administered survey is completed online, data will be stored as each question is answered. We anticipate that participants’ completing the self-administered survey on paper will be rare. When that happens, the paper forms will be stored in a locked cabinet until the data are entered by the research coordinator and data entry accuracy is verified by another study staff member, after which the paper forms will be shredded (Table 1).

**Table 1 Tab1:** Measurement instruments, constructs, and purpose {18a}

Instrument	Constructs	Measurement purpose
Addiction Severity Index	Demographics, alcohol and drug use, family planning methods, legal involvement, medical conditions, psychiatric disorders, employment, connection to community resources, family history, child custody adverse childhood experiences	Primary and secondary outcomes
Brief Version of Addiction Severity Index	Current alcohol and drug use, family planning, legal involvement, mental status, psychiatric disorders, employment, connection to community resources, child custody	Primary and secondary outcomes
Self-administered survey	Criminal justice involvement, expanded adverse childhood experiences (baseline only), social support, maternal attachment, post-traumatic stress, psychological distress, self-esteem, self-efficacy, addiction beliefs, positive parenting, knowledge of child development, benevolent child experiences, working alliance inventory	Secondary outcomes and mediators

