The 5^th^ edition of the Addiction Severity Index (ASI) is a semi-structured interview instrument that assesses the following domains: medical status, employment/support status, substance use, legal status, family history, family/social relationships, and psychiatric status [33]. This instrument has been supplemented with additional items developed by subject matter experts, straightforwardly worded. These include items to assess drug use during pregnancy, reproductive history, and adverse life experiences not assessed in the ASI. Substances assessed include and expand upon those in the ASI: alcohol, heroin, fentanyl, methadone, other opiates/analgesics, barbiturates, sedatives/tranquilizers, cocaine, methamphetamine, other amphetamines, cannabis, hallucinogens, inhalants, and other substances. Additional items assess birth control use, number and living situation of biological children, adverse life experiences, and child protective services involvement. Items have also been created to assess the services participants have received in the preceding year, including healthcare for mother and child(ren), family planning, mental health, housing, emergency funds, food/clothing/supplies, legal aid, domestic violence, childcare, support groups, public schools, and public health nursing. Each service is coded as to whether the participant expressed a need for that service (yes = 1/no = 0) and whether the service was received (yes = 1/no = 0). An abbreviated (brief) version of the ASI that omits time invariant/historical information is administered at the annual follow-up assessments.

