### Frequency and plans for auditing trial {23}

The trial is overseen by a group of investigators and a full-time Project Director at the University of Oklahoma and the University of Washington. A full-time research coordinator is responsible for data collection. This group oversees the implementation and evaluation of PCAP. The direct services are managed by a Supervisory/Manager in OU Outreach’s Southwest Prevention Center (SWPC). The Project Director meets weekly with the research coordinator and the investigator team, along with other meetings as needed. The investigator team and Project Director meet monthly with the SWPC to coordinate activities. The Direct Services team meets weekly with the SWPC Manager. The investigators meet weekly to closely monitor the PCAP trial and discuss the progress of the study and any issues that may arise during its conduct. Given the low-risk nature of the intervention, no external monitoring committee is used. The project also has a Parent Advisory Committee with their own leadership structure who meet quarterly with the full project teams. The Parent Advisory Committee also is invited to monthly investigator team meetings. They have advised on measurement, recruitment, retention, hiring, and direct services. They have also attended conferences and represented PCAP in public forums. We have no plans for an independent monitor.

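### The reason given for leaving all staff unblinded does not cover the research coordinator, the only named interviewer for the primary outcomes, so an avoidable assessor share of bias remains

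*Protocol article*

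**What the plan says.** The Blinding section of the protocol article states that "Group membership will not be blinded after assignment" and that "Participants and staff will be aware of whether a participant is assigned to the treatment or control group by necessity", because of what the intervention is. It does not distinguish staff who deliver PCAP from staff who measure outcomes. Concealment before assignment is described under Randomization procedures: "Neither the research staff using the system nor the participant will know the group assignment before the baseline data are collected". Nothing extends it past baseline.

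Three places identify who measures outcomes:

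- Frequency and plans for auditing trial: "A full-time research coordinator is responsible for data collection".
- Assessment procedures: participants complete assessments "connecting with the research coordinator via Zoom videoconferencing" where feasible, with the interview by phone otherwise.
- Data management: "During the interview portion of the assessment, the research coordinator will enter participant responses into REDCap as they are given".

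Table 1 assigns the primary outcomes to the Addiction Severity Index (ASI) and its brief version, which is used at the annual follow-ups. The text after the table says that the ASI "is a semi-structured interview instrument". The auditing section also gives direct services their own manager, in a unit separate from the investigator team.

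**The concern.** The necessity argument is sound for a participant who either has or does not have a case manager, and for the people who provide or supervise that service. Someone must also run the allocation. None of this applies to the person who asks about substance use, abstinence and contraception a year or more later. The questions are the same in both arms, and no primary outcome listed under Measures requires the interviewer to know the arm.

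The primary outcomes are obtained by self-report in a semi-structured interview, and the article plans no objective measure alongside it. Record linkage is mentioned in the Discussion only as a later possibility that depends on funding. If knowing the arm changes how an interviewer follows up or records an answer, nothing else in the plan would reveal or offset it. The trial's stated aims include ratings by federal evidence clearinghouses, so a primary contrast open to this challenge has a practical cost.

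**Working it through.** **Who needs to know the arm, set against the reason given**

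| Role | Does the nature of PCAP require knowledge of the arm? |
|---|---|
| Participant | Yes |
| Case manager and case-management supervisor | Yes; they deliver and monitor the service |
| Person who runs allocation | Yes, through the task itself |
| Research coordinator as follow-up interviewer | No reason is given, and none follows from the intervention |

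The article says that research staff use the randomization system but does not say which member does so. If it is the coordinator, that is a choice about task allocation, which can be changed.

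**The plan's own figures (Power and sample size)**

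Inputs: 200 participants with 1:1 allocation, so 100 per arm; d = 0.40; two-sided 0.05; and 132 completers, so 66 per arm, with d = 0.50. Stated power is 0.80 in both cases.

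- 100 per arm, d = 0.40: normal approximation 0.807, t-test 0.804.
- 66 per arm, d = 0.50: normal approximation 0.819, t-test 0.814.
- Completers: 200 × (1 − 0.33) = 134, against 132 stated.

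The figures reproduce. Masking the interviewer changes neither the sample size nor the power.

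**Illustration of what an assessment shift would do**

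The document gives no bias figure, so the shift b (in SD units) is assumed. With no true effect, n per arm and a z-test, the noncentrality is s = b / √(2/n), and the two-sided rejection probability is 1 − Φ(1.96 − s) + Φ(−1.96 − s).

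At n = 66, √(66/2) = √33 = 5.745:

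- b = 0.1: s = 0.574; rejection = 0.083 + 0.006 = 0.089.
- b = 0.2: s = 1.149; rejection = 0.209 + 0.001 = 0.210.

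Over a wider range:

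| Assumed b (SD) | 66 per arm | 100 per arm |
|---|---|---|
| 0 | 5% | 5% |
| 0.05 | 6.0% | 6.4% |
| 0.10 | 8.9% | 10.9% |
| 0.20 | 21.0% | 29.3% |
| 0.30 | 40.7% | 56.4% |

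A shift of 0.2 SD is 0.2 / 0.5 = 40% of the effect the trial can detect at its anticipated floor. The formula is symmetric in b: a shift against PCAP gives the same two-sided error under no effect and would mask a real benefit if there is one. It treats the outcome as continuous, whereas several primary outcomes are binary or counts.

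**Timing (Study design; Trial status)**

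Enrolment runs from December 2022 to an expected end in December 2024, so 36-month assessments fall between about December 2025 and December 2027. The protocol version is dated 14 November 2023, before the first 12-month visit was due.

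**The case against.** The strongest counter-argument is that masking the interviewer may achieve little. Participants know their arm and report every primary outcome themselves. The interview also covers services received, after up to three years of roughly biweekly contact with a case manager, so many will reveal their arm. A coordinator who learns it at 12 months still knows it at 24 and at 36 months, the primary endpoint. The separation between teams is only partial: the Project Director meets the coordinator weekly, and the investigators and Project Director meet the service unit monthly. All of this stands. It limits what masking can deliver, but it does not make the interviewer's knowledge of the arm necessary.

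A reader might also infer more than the text supports:

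- That the interviewer has discretion over coding. The article says only that the ASI is semi-structured. It describes the added items as plainly worded and says answers are keyed as given; most primary items are factual.
- That the bias would favour PCAP. Nothing fixes a direction, since either arm could be questioned more closely.
- That one person conducts every interview. The coordinator is the only interviewer named, which makes this a reasonable inference, but no sentence says it.
- That only participants and case managers need the arm. The supervisor and the person running allocation need it too.

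The Discussion does acknowledge reliance on self-report, but as a limitation of the data source. It does not mention unblinded assessment.

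**Conclusion.** The point holds in a limited form. The article makes a positive decision to unblind all staff and gives a reason that does not reach the follow-up interviewer. Part of the resulting bias can be avoided; the part that comes from unblinded participants cannot.

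The size of the avoidable part is unknown. The 9% and 21% error rates at 66 per arm show the sensitivity of the primary contrast to assumed shifts of 0.1 and 0.2 SD. They attribute the whole shift to the assessor and are not evidence that such a shift exists. The conclusion rests on two readings of the text: that the coordinator conducts the follow-up interviews, since nobody else is named, and that the staff described as aware of the arm include the coordinator, since no exception is made. The change is worth making because it is cheap and most of the primary-endpoint interviews are still to come at the stated protocol version.

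**What to change.** 1. Reword the Blinding section so that necessity applies to participants, service staff and the person who runs allocation.
2. Have an existing member of the research staff who does not interview participants trigger REDCap randomization after baseline and notify the participant. This should not be the case-management team, because allocation would then sit with those who carry the caseload.
3. Hide the allocation field from the coordinator through REDCap user rights, and keep arm-level information out of meetings the coordinator attends. This matters particularly if the Project Director takes on the allocation task.
4. Open each follow-up with a scripted request not to disclose the arm, and ask the primary-outcome items before those on services received.
5. Record at each follow-up whether the coordinator has become unmasked, and how.
6. Report unblinded assessment as a limitation for participants whose arm the coordinator already knows.

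The cost is a permissions change, a short script, one added field and the transfer of one task between existing staff; no extra assessor is needed. The downside is that masking will be incomplete, especially for those already enrolled and after any disclosure at 12 or 24 months, so the 36-month data will mix masked and unmasked assessments. The unmasking record lets the report show that mix.
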